# Effect of electroacupuncture versus solifenacin for moderate and severe overactive bladder: a multi-centre, randomized controlled trial study protocol

**DOI:** 10.1186/s12906-020-03018-y

**Published:** 2020-07-16

**Keywords:** Electroacupuncture, Solifenacin, Overactive bladder, Randomized controlled trial

## Abstract

**Background:**

Overactive bladder is defined as “urgency, with or without urge incontinence, usually with frequency and nocturia”. Electroacupuncture may be a safe and an effective alternative therapy for overactive bladder, but the evidence is limited.

**Methods:**

We will conduct a three-arm, non-inferiority, multi-centre randomized controlled clinical trial. A total of 420 patients with moderate and severe overactive bladder will be randomly assigned to one of three groups: the electroacupuncture group (*N* = 140), sham electroacupuncture group (*N* = 140), and solifenacin group (*N* = 140). The primary outcome will be the change in the overactive bladder symptom score from baseline to the end of the 12-week treatment. The secondary outcomes will include the proportion of participants with a decrease in the overactive bladder symptom score ≥ 3 at weeks 4, 8, 12, 20, and 32; the change in average 24 h values of urination, nocturnal urination, urgency incontinence and urgency episodes from baseline to weeks 4, 8, 12, 20 and 32, and so forth. The adverse events will be recorded. Statistical analysis will include covariance analysis, nonparametric tests and descriptive statistics.

**Discussion:**

This study will answer the question of whether electroacupuncture is effective and non-inferior to solifenacin for improving the symptoms of overactive bladder patients.

**Trial registration:**

Chinese clinical trial registry (ChiCTR1800019928).

## Background

Overactive bladder, also known as OAB, or overactive bladder syndrome, is defined as “characterized by urinary urgency, with or without urgency urinary incontinence, usually with increased daytime frequency and nocturia, if there is no proven infection or other obvious pathology.” by the International Continence Society (ICS) [1]. The detrusor can be considered hyperactive on urodynamics in some patients. The guidelines for the diagnosis and treatment of OAB in adults were first presented by the American Urological Association (AUA) in 2012 [2] and updated in 2015, where the definition of OAB is consistent with that of ICS but emphasizes the exclusion of neurogenic bladder [3]. According to the first large population-based study of OAB conducted in six European countries using the 2002 ICS definitions, the prevalence of OAB was 11.8% (10.8% men; 12.8% women) among people aged 40–64 years [4]. China’s first large-scale epidemiological survey of OAB showed that for people over 18 years old, the overall prevalence was 6% and was 11.3% for people over 50 years old, which increasing with age [5]. OAB, with a severely negative impact on patients’ mood and health, increases both economic and social burden [6].

The latest guidance from the AUA in 2015 classifies OAB treatment regimens into first-line, second-line, third-line and others. The first-line treatment consists of behavioural modifications, such as bladder training, bladder control strategies, pelvic floor muscle training, and fluid management. Second-line treatment consists of pharmacologic management, mainly drugs are antimuscarinic (AM) agents and β3-adrenoceptor agonists. Solifenacin is an AM, especially a specific competitive inhibitor of the M3 subtype, and is one of the most commonly used drugs for the treatment of frequent urination, urgent urination, nocturia and urgency urinary incontinence in patients with OAB [7]. Intramuscular injection of botulinum toxin type A into the detrusor muscle, percutaneous tibial nerve stimulation (PTNS), and sacral neuromodulation (SNS) are types of third-line treatments. The other treatment is surgery [3].

Behavioural modifications pose few risks to patients, but the efficacy depends on the positivity and persistence of patients [8]. As second-line treatments, antimuscarinic agents can lead to many adverse effects, including dry mouth, blurred vision, constipation, and so on. And the tachycardia, hypertension, headache and other adverse reactions may occur with the beta-3-receptor agonists. Inefficacy and adverse events are the most common reasons for the withdrawal of AM [9]. A retrospective cohort analysis indicated that adherence rates to AM ranged from 27.6 to 40.4% over 12 months [10]. In terms of SNS, a systematic review [11] showed that this treatment could significantly reduce the episodes of urination and urinary incontinence and could reduce the use of pads; however, the complications after implantation include pain at the stimulation site, infection and changes in intestinal function. PTNS is the other treatment for OAB that has been confirmed to improve symptoms [12].

As a main branch of traditional Chinese medicine, acupuncture has been recommended for solving neurogenic bladder dysfunction by the World Health Organization [13]. Our team’s latest OAB system evaluation suggests that electroacupuncture (EA) may reduce urinary frequency, urinary incontinence, and nocturnal urination episodes [14]. However, the evidence does not support the efficacy of EA alone in the treatment of OAB. In the future, high-quality research methods and large sample sizes are needed to confirm the efficacy of EA in OAB. EA is similar to PTNS in some ways; however, the type of EA treatment used in this trial could stimulate not only the tibial nerve (through the acupoint of SP6) but also the 3 sacral (through the acupoint of BL33) and pudendal nerves (through the acupoint of BL35). Integrating PTNS and SNS stimulation points may have good benefits. Some research has been conducted to prove the effectiveness of EA for the treatment of OAB. A study conducted by LU Yujin et al. included 86 OAB patients with EA, and the results showed an overactive bladder symptom score (OABSS) of 8 (CI: 7–9) before treatment and 2 (CI: 4–6) after treatment, with a statistically significant difference (*P* < 0.05) [15]. A randomized controlled trial (RCT) conducted by Wang Yafei et al. suggested that EA had significant clinical efficacy for OAB with a simple operation, and there were no side effects or postoperative complications, which was better than the medicine [16]. Another animal experiment proved that EA could effectively inhibit bladder overactivity, and the effect had acupoint specificity [17].

Thus, based on the aforementioned historical study and clinical experience, our team designed this prospective, multi-centre, RCT study protocol with a large sample size to evaluate the effectiveness and safety of EA compared with solifenacin for OAB.

## Methods and design

### Aims, design, and study setting

#### Primary objective and study hypothesis

The primary objective is to assess the effect of EA on the treatment of OAB. We hypothesize that EA will be effective and non-inferior to solifenacin for improving the symptoms of OAB patients.

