### Randomization and blinding

After the 1-week assessment has been carried out and informed consent has been obtained, participants will be divided into the EA group, SA group or solifenacin group at a ratio of 1:1:1 due to the completely randomized block design of the hospital factor. Randomization will be generated by the central random system based on the computer network. Randomized numbers and groupings will be applied by research assistants who are not involved in the treatment or evaluation. Patients in the EA group and the SA group will be blinded, while those in the solifenacin group will be subjected to open trials. In the informed consent signed before the participants were enrolled, we will inform them that there are two types of acupuncture in addition to the drug group, and participants will be required to complete the entire trial cycle no matter which group they are assigned to. After the last treatment, the evaluation for the blinding of acupuncture will be tested within 5 min in the EA and SA groups. The results of this evaluation will be used to analyze the effect of blinding on the trial outcome measures. Efficacy evaluation and data entry will be performed by research assistants who are not involved in the grouping. The statisticians, outcome assessors, and physicians will be blinded to the allocation during data summarization.

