### Outcome measures

In this study, there will be one primary outcome and nine secondary outcomes. These are presented in Table 1. All adverse events will be recorded. The OABSS is widely used as a primary outcome measure in OAB studies, as it is safe and convenient and has been proven to have good reliability and validity in OAB [22]. The OABSS is comprised of 4 test items including frequency of urination, nocturia, urgency urinary incontinence and urgency episodes in 24 h. Total score ranges from 0 to 15, with scores of 3 to 5 indicating mild OAB, 6 to 11 indicating moderate OAB, and 12–15 indicating severe OAB. The secondary outcomes are based on 7-day bladder diaries and the OAB-q. A previous study suggested that 7-day bladder diary provided more accurate information regarding incontinence than a 3-day diary [23], in which we will evaluate the average episodes of 24 h urination, nocturia, urge incontinence and urgent urination changes from baseline. The OAB-q, with 33 questions about sleeping, anxiety, trouble in life and so on, is appropriate for assessing symptomatic distress or assessing the impact of OAB on health-related quality of life [24].

**Table 1 Tab1:** Outcome measures

	Outcome measure	Time point	Description	Statistics
Primary outcome	Change in OABSS from baseline to the end of week 12	Week 12	Calculated based on the OABSS.	Modified t-test
Secondary outcomes	Change in OABSS from baseline to the end of weeks 4, 8, 20, and 32	Weeks 4, 8, 20, and 32	Calculated in the same way as the primary outcome.	Covariance analysis or non-parametric test
	Proportion of participants with a decrease in the OABSS of ≥3	Weeks 4, 8, 12, 20, and 32	The number of patients with a reduction in OABSS ≥3 divided by the number of participants at baseline.	A chi-square test or Fisher’s test
	Change in 24 h urination/nocturia/urgency urinary incontinence /urgency episodes from baseline	Weeks 4, 8, 12, 20, and 32	The average 24 h urination/nocturia/urgency urinary incontinence /urgency episodes equal to the sum of urination/nocturia/urgency urinary incontinence/urgency episodes divided by 7.	Covariance analysis or non-parametric test
	Change in OABSS for each question from baseline	Weeks 4, 8, 12, 20, and 32	Calculated based on the OABSS for each question.	Covariance analysis or Non-parametric test
	Change in OAB-q from baseline	Weeks 4, 8, 12, 20, and 32	Calculated based on the OAB-q.	Covariance analysis or non-parametric test

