### Sample size calculation

The sample size will be calculated based on previous studies conducted by Zhao Y et al. [14, 25]. A sample size of 420 patients will provide 80% power (α = 0.05) to detect a non-inferiority effect of EA therapy on the primary outcome, assuming a 10% loss. The non-inferiority margin will be 50% of the comparative efficacy between SA and solifenacin. The non-inferiority margin will be set based on our hypothesis that EA will be associated with at least 50% of the difference in efficacy of solifenacin compared with SA.

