### Statistical analysis

Statistical analysis will be conducted by independent third-party professional statisticians. We will use a modified t-test based on the retention of the effect method to analyse whether EA is non-inferior to solifenacin [26]. If the lower boundary of the confidence interval around the mean difference between the numbers in the EA group versus the solifenacin group exceed 50% of the mean difference between the numbers in the solifenacin group and the SA group, then non-inferiority will be claimed. The intention-to-treat (ITT, randomized participants) and per-protocol datasets (PP, ITT participants who received at least one treatment session) will be used to analyse the primary outcome. Missing data will be filled with a multiple imputation method under the missing-at-random assumption. Secondary outcomes will be calculated with observed values. Categorical data will be described by case number and percentage and will be analysed with Fisher’s exact test or the Chi-square test where appropriate. Continuous data will be described as the mean ± standard deviation, median, maximum and minimum values, and comparisons between groups will be conducted by covariance analysis or nonparametric tests where appropriate. A P (2-tailed) value less than or equal to 0.05 will be considered statistically significant. Statistical Package for the Social Sciences (version 13.0; SPSS; Chicago, Illinois, USA) will be used to perform the statistical analysis.

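### The primary analysis names no EA-versus-sham test for the 'effective' half of the hypothesis, and its 50% retention rule can be met without solifenacin beating sham

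*Protocol article*

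**What the plan says.** The section on the primary objective states a double hypothesis: "We hypothesize that EA will be effective and non-inferior to solifenacin for improving the symptoms of OAB patients".

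The primary outcome in Table 1 is "Change in OABSS from baseline to the end of week 12", and the only statistic listed for it is the modified t-test. The Statistical analysis section gives that test one purpose: "We will use a modified t-test based on the retention of the effect method to analyse whether EA is non-inferior to solifenacin". The decision rule in the same section sets the lower confidence limit for EA minus solifenacin against a yardstick taken from the trial itself, and it closes as follows: "50% of the mean difference between the numbers in the solifenacin group and the SA group, then non-inferiority will be claimed".

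The Sample size calculation section sets the yardstick: "The non-inferiority margin will be 50% of the comparative efficacy between SA and solifenacin". It also says "A sample size of 420 patients will provide 80% power", and it attaches that power to non-inferiority only.

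Sham electroacupuncture (SA) therefore enters the primary analysis only through the margin. The article does not name an EA-versus-SA or solifenacin-versus-SA test of the primary outcome, does not set a testing order, and does not say what follows if solifenacin fails to beat sham.

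**The concern.** A retention test asks whether EA keeps at least half of what solifenacin gains over sham. The question makes sense only if solifenacin gains something. The published rule takes the in-trial solifenacin-minus-sham difference as it comes, with no condition that it be positive. If that difference is negative, half of it is no longer an amount of efficacy to retain, yet the rule still returns a verdict.

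The design gives some reason to guard against this. On blinding: "Patients in the EA group and the SA group will be blinded, while those in the solifenacin group will be subjected to open trials". Sham patients attend as many sessions as EA patients (28 over 12 weeks) and feel a slight current. The Background reports low adherence to antimuscarinic drugs. Each of these could narrow or reverse the solifenacin-minus-sham difference.

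What is at stake is the headline conclusion. A reader given a non-inferiority result under a hypothesis that also says *effective* will take it as evidence that EA works. The named primary analysis does not secure that inference, although a 140-patient sham arm is enrolled that could.

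**Working it through.** **Inputs from the protocol.** 420 patients at 1:1:1, so 140 per arm; 10% loss; 80% power; α = 0.05; margin 50% of solifenacin minus SA. The loss arithmetic is consistent: 140 × 0.90 = 126 evaluable, and 126 / 0.90 × 3 = 420.

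**Not given.** No SD, mean difference or numeric margin is stated, so 420 cannot be reproduced and all effects below are in SD units. The sidedness of the non-inferiority test is not stated either. One-sided 0.025 is used first and one-sided 0.05 as a check. Normal means and equal SDs are assumed.

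**Step 1, the contrast.** Let E, S and P be the mean improvements on EA, solifenacin and SA. Retaining 50% means E − S > −0.5(S − P), which rearranges to

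E − 0.5S − 0.5P > 0.

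Its standard error is √[(1 + 0.25 + 0.25)/126] = √(1.5/126) = 0.109 SD.

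**Step 2, the design effect implied by 80% power.** If E = S, the contrast is 0.5(S − P). So S − P = 2 × (1.96 + 0.842) × 0.109 = 0.611 SD. At one-sided 0.05 the figure is 0.543 SD.

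**Step 3, EA no better than sham.** Put E = P and let solifenacin be g SD below sham. The contrast becomes 0.5g, which is positive whenever g > 0. The claim rate is Φ(0.5g/0.109 − 1.96). One million simulated trials per scenario agree with the formula.

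| Solifenacin vs sham (assumed) | Claim rate, one-sided 0.025 | One-sided 0.05 |
|---|---|---|
| 0.3 SD better | 0.04% | 0.13% |
| equal | 2.5% | 5.0% |
| 0.1 SD worse | 6.7% | 11.8% |
| 0.2 SD worse | 14.8% | 23.3% |
| 0.3 SD worse | 27.9% | 39.4% |
| 0.5 SD worse | 63.0% | 74.1% |

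**Step 4, sensitivity to how the rule is read.** Suppose the rule compares the lower confidence bound of E − S with −0.5(S − P), taking the margin at its point estimate. The contrast must then exceed 1.96 × √(2/126) = 0.247, and the rates at 0.2 and 0.3 SD fall to 8.9% and 18.7%. Taken with the literal sign (+50%, improvement scale), they rise to 62.5% and 88.8%. The sign is a separate matter. All three readings share the pattern in the table.

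**Step 5, adding the sham comparisons (one-sided 0.025).** With EA > SA required as well, the claim rate when EA equals sham is 2.4% at 0.2 SD, 2.5% at 0.3 SD, and never more than 2.5%. With solifenacin > SA also required, it is 0.06% when all arms are equal and about 0% at 0.2 SD or more.

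**Step 6, cost.** At E = S = P + 0.611 SD, each superiority test has power Φ(0.611/0.126 − 1.96) = 99.8%, where 0.126 = √(2/126). Simulated power for the retention claim is 80.02% with no prior test, 80.02% with EA > SA required, and 79.86% with both required. At one-sided 0.05 and 0.543 SD it is 79.98% with no prior test and 79.67% with both.

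**The case against.** **A reader might infer that efficacy against sham is tested nowhere.** The article does not support that. The Statistical analysis section provides generally for between-group comparisons of continuous data. Table 1 lists between-group tests for OABSS change at weeks 4, 8, 20 and 32, and for the proportion with a fall of at least 3 points at every visit including week 12. EA versus SA could fall within these. What stands is that no such comparison is named, ordered or tied to the word *effective* for the primary outcome.

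**A reader might infer that the rule inflates false non-inferiority claims.** It does not. If EA equals sham and solifenacin is 0.3 SD below sham, EA really is 0.3 SD better than solifenacin, and calling it non-inferior is true. What is lost is assay sensitivity and the inference that EA works.

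**A reader might infer that solifenacin is likely to fall below sham.** No figure in the article supports that, and the margin text presumes a positive difference. If solifenacin truly beats sham, passing the retention criterion already implies that EA beats sham. If the two are equal, the error stays at 2.5%.

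**Testing order is often left to the SAP,** which is not shown, and the cited retention method may carry its own prerequisite, which cannot be checked here. This has force, but only in part. The article does not stay silent on the rule: it states the condition under which non-inferiority will be claimed, and that condition omits any comparison with sham.

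**Requiring solifenacin > SA makes the conclusion lean on an open-label drug versus sham-needle comparison.** That is fair. EA > SA alone already caps the claim rate at 2.5% when EA equals sham, so it should come first. The solifenacin comparison is needed for the narrower question of whether half of its effect is a meaningful yardstick.

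**Conclusion.** The point holds for the primary analysis. Half of the hypothesis has no named primary test, and the stated non-inferiority rule can be met when its yardstick has lost its meaning.

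The size depends wholly on how far solifenacin falls below sham, which the article gives no basis for estimating. With EA equal to sham, the claim rate is 2.5% at no shortfall, and 14.8% or 27.9% at assumed shortfalls of 0.2 or 0.3 SD. These figures rest on 126 evaluable per arm, one-sided 0.025, equal SDs and the contrast EA − 0.5 × solifenacin − 0.5 × SA. They are rates of uninformative claims, not of false statements about EA against solifenacin.

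The sham arm already provides the data to close the gap, so the change should be made before unblinding.

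**What to change.** Prespecify an ordered analysis of the week-12 OABSS change in the Statistical analysis section and Table 1:

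1. Test EA superior to SA at two-sided 0.05. Base any claim that EA is effective on this test.
2. Only if step 1 succeeds, test 50% retention against solifenacin, with its sidedness stated.
3. Test solifenacin superior to SA at two-sided 0.05, as the assay-sensitivity condition for interpreting step 2. If it fails, report that the 50% retention claim cannot be interpreted.

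**Cost.** No alpha split and no extra patients; 420 stands. At the back-solved effect of 0.611 SD, power falls from 80.02% to 79.86% with both sham comparisons required, a loss of less than 0.2 of a percentage point. There is no visible loss if only EA > SA is required. The real price is interpretive: if solifenacin does not beat sham, the trial can still report on EA versus sham but must give up the retention claim.

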#### Study design

This study will be a multi-centre, randomized, parallel group, and three-arm clinical trial. It will be conducted from September 2019 to June 2021 in 4 hospitals around China. If the study is not expected to be completed on time, 2 research hospitals will be added or replaced. Participants with OAB will be recruited via posters, television, websites and outpatients and will then be screened according to the eligibility criteria. A total of 420 participants will be ultimately enrolled. Prior to enrolment, all participants will voluntarily sign the informed consent form that has been approved by the ethics committee. Randomization will be performed centrally by the Clinical Evaluation Centre of the China Academy of Chinese Medical Sciences in Beijing, and eligible participants will be randomized to the EA group, sham electroacupuncture (SA) group or solifenacin group at a 1:1:1 allocation ratio. A randomization number will be applied after enrolment. The statisticians, outcome assessors, and participants in the EA and SA groups will be blinded to the allocation. A flowchart demonstrating an outline of the study is included in Fig. 1.

**Fig. 1 Fig1:**
[figure not shown]
The flowchart

#### Study setting

This study will be conducted at the West China Hospital of Sichuan University, Chongqing Hospital of Traditional Chinese Medicine, Subei People’s Hospital of Jiangsu Province, and Jiangbin Hospital of Guangxi Zhuang Autonomous Region. Among them, three are Western medicine hospitals and one is a traditional Chinese medicine hospital.

### Ethics

This trial protocol (version no.20180821, date 9th October,2018) is in accordance with the ethical standards described in the 2013 updated Declaration of Helsinki [18]. All research units have been reviewed by the West China Hospital of Sichuan University clinical trials and biomedical ethics committee before the start of the clinical study (the ethical approval number is 2018–386). The study has also been registered at http://www.chictr.org.cn (ChiCTR1800019928). The study will be reported in compliance with the CONSORT statement (www.consort-statement.org) as well as the standards for reporting interventions in clinical trials of acupuncture (STRICTA) [19, 20].

